**Discussion:**

PEARL is an intervention based on self-determination theory, designed to reduce depression in newly admitted residents by tailoring day to day care to meet their psychological needs. This simple psychological approach offers an alternative care model to the current over-reliance of antidepressant medications.

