### Sample population and recruitment procedure

RAC facilities (known internationally as nursing homes, assisted living facilities, or long-term care facilities) across metropolitan Melbourne, Australia with a minimum of 50 resident places are being approached to participate in the study. Facilities are randomly allocated to the intervention or control condition by a biostatistician not otherwise involved in delivery of the intervention or data collection. Randomisation of facilities is conducted using a web-based random allocation sequence generator (https://www.random.org/) and stratified by organisation and number of resident places (< 100 vs 100+), to ensure that each condition contains a spread of different organisations and facility sizes, with these organisational factors considered potential contributors to study outcomes. Facilities are randomised upon enrolment into the study, before data collection begins.

Participating facilities are informed of the condition to which their facility has been allocated and asked to nominate residents who are potentially suitable to participate in the trial. Inclusion criteria are (i) aged 60 years or above; and (ii) admitted to the RAC facility within the previous 4 weeks. Exclusion criteria are (i) acute severe medical illness likely to compromise participation in the program; (ii) moderate-severe cognitive impairment, operationalised as a Mini-Mental State Examination (MMSE) score of less than 15 [16]; and (iii) non-fluency in English. Residents at all levels of depression, as well as those without symptoms of depression, are eligible to participate.

Facility staff are asked to identify residents who meet the inclusion criteria and who have an absence of severe cognitive impairment and notify the research team. These residents are then are approached by a researcher for consent and eligibility screening, including administration of the MMSE [16]. Consent is obtained from the participant, as well as by their next-of-kin in cases where the MMSE score is less than 24. Participants are blind to their study condition until after they have consented. Research assistants collecting outcome data are also blind to study condition, with a process in place to record instances where they become unblinded, for example, through disclosure by the participant or facility staff.

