Session 1	Validation, orientation and social relations	Resident
• Introduction to PEARL • Validating and normalising the resident’s experience of relocating to the facility • Orientation to the facility and broader community • Relationships with family and friends • Forming relationships with other residents		
Session 2	Increasing meaningful activity and enhancing competence	Resident
• Understanding the resident’s previous activities, occupation, skills, and interests • Assessing preferences for day to day activities, using a structured tool to determine those that enhance competence • Developing an implementation plan to increase meaningful activity		
Session 3	Enhancing autonomy	Resident
• Assessing preferences for level of choice, independence and autonomy in their environment and day to day activities, including care tasks, using a structured tool • Developing a plan to increase autonomy		
Booster 1	Review and problem-solving	Resident and staff member
• Introducing the role of the staff member in supporting the resident in meeting their goals • Reviewing the program, individual strategies selected for implementation, and the resident’s progress in meeting goals • Reinforcing successes and problem-solve solutions to address barriers, using a problem-solving approach and refining strategies if required		
Booster 2	Review and problem-solving, and future planning	Resident and staff member
• Reviewing the program, reinforcing resident’s successes and achievements. • Providing assistance in problem-solving any difficulties reported by resident. • Preparing for the future: How to apply the PEARL approach to deal with future issues that emerge.		

Clinicians delivering the program have previous experience in delivering psychological treatments and receive training and regular supervision in implementing the intervention. Treatment fidelity is monitored using a review of audiotaped sessions, with sessions coded for adherence to the intervention manual. The review will be undertaken on 5% of sessions randomly selected from all sessions.

Participants in the control group do not receive any additional intervention beyond the usual care offered by the facility. This includes group leisure activities, assistance with care, and medications, which are provided to participants in both intervention and control groups.

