Several variables are assessed as potential mechanisms of change (mediators), relating to the targets of the intervention, including satisfaction of basic psychological needs (autonomy, competence and social relations), which is assessed using the 21-item Basic Needs Satisfaction in Life Scale [31]. A 15-item Importance of Basic Needs Scale was developed specifically for this study to assess residents’ perceptions of the importance of these three basic psychological needs. The Meaningful Activity in Residential Care Scale is a 9-item scale designed for this study to assess the degree to which residents feel they have the opportunity to engage in meaningful activity. A scale was also developed to assess residents’ perception of their relocation to RAC: the 12-item View of Relocation Scale, which is assessed at T1 as a potential moderating variable. This scale assesses the degree to which the resident perceives they had control in the decision to relocate to RAC and the degree to which the resident perceives that the relocation was warranted. The three scales constructed for the purposes of the current study have not been previously validated; however, psychometric evaluation of the scales will be reported in subsequent publications reporting trial results. Copies of the scales are available in the supplementary files.

The following resident demographics are recorded at baseline: age, gender, and admission date. Resident cognition is assessed using the Mini Mental State Examination [16] during screening, and also at T4 to account for changes during the study period. Medical and psychiatric history, including pharmacological and non-pharmacological treatments for depression are obtained from the resident’s file at each time point, while the resident will indicate self-rated health at each interview using items 1 and 2 from the Physical Functioning Scale of the Short-Form 36 [32]. Facility characteristics (staff: resident ratio, staff turnover, number of resident places, type of facility) are obtained directly from the participating facility managers. In addition, the Sheltered Care Environment Scale [33] is administered to a random sample of between 4 and 10 staff at each facility as a measure of organisational climate.

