### Statistical analysis

Prior to statistical analysis, data entry will be checked through a random sample of baseline assessments that are entered twice; if data entry is found to be problematic (less than 99% concordance rate), double data entry will be employed for all assessment data. In addition, frequencies will be generated for all variables, to ensure valid range values have been entered.

Descriptive statistics will be used to summarise baseline characteristics and pattern of change in participants over time. Primary analyses will be on an intention to treat basis, with supplementary ‘per protocol’ analyses. To account for the within-facility clustering of participants and repeated assessments, differences in the outcomes of the intervention and control groups will be compared with multilevel modelling [34]. For each outcome, a separate three-level model will be specified, with repeated measurements as level 1, individuals as level 2, and RAC facilities as level 3. The models will include group allocation, assessment time, and group by time interaction as predictors, medication use at each assessment time, and organisational climate and facility size < 100/100+ (both measured at the level of a RAC facility) as covariates. Individual and RAC facility variables will be modelled as random effects and the remaining variables will be modelled as fixed effects. Supplementary analyses will test treatment allocation by cognitive impairment interaction to examine whether the effect of intervention differs according to the presence of cognitive impairment. To explore the mediational role of autonomy, competence, and social relations on the association between intervention and depression, multilevel path analysis (with individuals clustered within RACFs) will be undertaken, controlling for organisational climate. In all analyses, missing data will be assumed to be missing at random and will be handled with conditional maximum likelihood estimation. The impact of possible non-random attrition will be explored with simulation analyses [35].

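### The primary model, labelled intention to treat, adjusts for medication use measured after allocation, so it does not estimate the total effect of PEARL versus usual care

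*Protocol article*

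**What the plan says.** All references are to the protocol article.

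- **Statistical analysis.** "Primary analyses will be on an intention to treat basis". For each outcome there is one three-level model: "The models will include group allocation, assessment time, and group by time interaction as predictors". The covariates are "medication use at each assessment time, and organisational climate", plus facility size. No primary model without these covariates is described.
- **Outcomes.** Details of "pharmacological and non-pharmacological treatments for depression are obtained from the resident’s file at each time point", and Table 2 marks T1 to T4. T2, T3 and T4 are at weeks 8, 16 and 31. T3 is named there as the primary endpoint.
- **Intervention.** The last resident session is in week 7. On usual care: "This includes group leisure activities, assistance with care, and medications, which are provided to participants in both intervention and control groups".
- **Abstract, Discussion paragraph.** PEARL "offers an alternative care model to the current over-reliance of antidepressant medications".
- **Hypotheses and expected outcomes.** The comparison of interest is PEARL added to usual care against usual care alone.
- **Climate.** The Sheltered Care Environment Scale "is administered to a random sample of between 4 and 10 staff at each facility as a measure of organisational climate" (Outcomes); no date is given. "Facilities are randomised upon enrolment into the study, before data collection begins" (Sample population and recruitment procedure). That section also says facilities are told their condition.

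**The concern.** A covariate measured after allocation is safe in a treatment comparison only if allocation cannot move it, directly or through the outcome. Concurrent medication does not meet that condition. Prescribing can respond to depression, which PEARL aims to reduce, and the article presents PEARL as an alternative to reliance on antidepressants. Once medication at T2 to T4 is in the model, the group-by-time coefficient compares residents with the same current medication use. That answers a different question from the stated hypothesis. The published effect could be smaller or larger than the effect of allocation, and the article names no unadjusted primary result against which to see this.

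**Working it through.** **1. The plan's own figure.** Inputs from Sample population and recruitment procedure: 22 facilities, 14 residents each, ICC .054, 25% attrition, d = .48, two-sided 5%. A 1:1 allocation is assumed because no ratio is stated.

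- Analysed: 308 × .75 = 231.
- Design effect: 1 + (14 − 1) × .054 = 1.702.
- Effective n: 231 / 1.702 = 135.7.
- z = .48 × √(135.7 / 4) = 2.796.
- Power = Φ(2.796 − 1.960) = 79.8%.

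The stated 80% reproduces. The calculation has no medication term, so removing post-baseline medication leaves it unchanged.

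**2. Timing.** The last PEARL session is in week 7. T2 is week 8, T3 week 16 and T4 week 31, so three of the four medication values in the model post-date both allocation and the intervention. Only T1 precedes the resident's PEARL sessions.

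**3. How adjustment moves the estimate.** In a single linear regression, with negative values meaning benefit:

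adjusted effect = total effect − β × Δ,

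where β is the medication coefficient given group and Δ is the difference in medication prevalence (PEARL minus control). The article gives neither, so both are assumed. With a total effect of −.48:

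| Δ | β = −.4 | β = +.4 |
|---|---|---|
| 0 | −.48 | −.48 |
| −.05 | −.50 | −.46 |
| −.10 | −.52 | −.44 |
| −.20 | −.56 | −.40 |

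For example, −.48 − (.4)(−.10) = −.44. β is negative if medication mainly relieves symptoms and positive if it mainly marks residents who are worse. The sign of β sets the direction.

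**4. Simulation of the planned type of model.** There are four visits, a random person intercept, and group, time and group by time, with and without time-varying medication. All prescribing inputs are assumptions.

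*Medication has no effect and responds to symptoms* (person variance .6, error variance .4, log odds of medication = −.2 + b × symptoms, facility level omitted, true d = .48):

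| Prescribing follows | b = 1 (OR 2.7 per SD) | b = 1.5 (OR 4.5 per SD) |
|---|---|---|
| Prior-visit symptoms | about .48 | about .48 |
| Same-visit symptoms | about .43 | about .40 |

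A version with the facility level (ICC .054) and medication following earlier symptoms gave shifts of only .002 to .010 SD.

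*Medication helps and PEARL lowers its use at T3 from 40% to 22%* (three-level model):

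| Benefit of medication | Direct PEARL effect | Total effect | Adjusted estimate | Difference |
|---|---|---|---|---|
| .2 SD | −.48 | −.440 | −.475 | −.035 |
| .4 SD | −.48 | −.406 | −.475 | −.070 |
| .4 SD | 0 | +.074 | +.005 | −.070 |

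The identity in step 3 agrees: β × Δ = (−.2)(−.18) = .036 and (−.4)(−.18) = .072. In the last row, a net harm from reduced medication is reported as about zero.

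*Medication affected neither by allocation nor by symptoms:* the shift is 0.

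**The case against.** **The link from PEARL to medication is inferred.** No session in Table 1 concerns medication, no hypothesis predicts reduced use, and medication is part of usual care in both arms. This stands as a limit on how large the bias might be. It does not rescue the term, because medication can also move through symptoms, which PEARL is meant to change.

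**Intention to treat means analysing residents as allocated, and covariates do not break that.** That is correct about the analysis set. The fault is that the coefficient no longer estimates the total effect of allocation, which is what the hypothesis asks for.

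**Stronger readings that the article does not support:**

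- *A marked loss of effect in every case.* Regressing T3 symptoms on group and medication alone, under the same assumptions, gives about .43 and .40 for prior-visit prescribing (b = 1 and 1.5) and .40 and .35 for same-visit prescribing, with power of about 72% at b = 1 same-visit. The plan specifies a repeated-measures model. There the prior-visit loss is at most about 1%, and power at b = 1 is about 74% (same-visit) or 79% (prior-visit). Medication is read from the resident's file, so much of it may reflect earlier prescribing.
- *Bias usually towards no effect.* This follows only if medication is taken to do nothing. If it helps and PEARL reduces it, benefit is overstated.
- *Climate is a consequence of treatment.* The article places its collection after allocation. It does not date it relative to PEARL starting at a facility or show that PEARL changes it. The raters are a random sample of staff, not specifically those working with the clinician.

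**Conclusion.** The medication term is wrong as written. A primary analysis meant to compare PEARL plus usual care with usual care alone conditions on a variable that post-dates allocation and can be affected by it. This holds whatever the size of the bias.

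The size and direction cannot be obtained from the article. Across the repeated-measures scenarios, the outcome ranges from no material change in d = .48, through a fall to about .43 to .40, to benefit overstated by .035 to .070 SD. The fall needs prescribing that strongly tracks same-visit symptoms. The overstatement needs effective medication and an 18-point drop in its use. The argument takes the medication covariate to be, or to include, treatment for depression, as recorded under Outcomes.

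Organisational climate is a secondary and conditional point: a risk arising from collection after allocation, not a demonstrated bias. Facility size is a stratification factor and raises no difficulty.

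**What to change.** 1. In the primary model, replace the time-varying medication covariate with medication use at T1.
2. Report medication use at T2, T3 and T4 by arm as an outcome, so that any change in prescribing is visible.
3. Keep the model with time-varying medication as a supplementary analysis, described as an effect at given concurrent medication use.
4. State when organisational climate is measured at each facility. Keep it in the primary model only if that was before PEARL could affect staff there; otherwise move it to a supplementary model.

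The cost is a change of wording. T1 medication is already collected (Table 2), no new data are needed for items 1 to 3, and the sample size calculation is untouched at 79.8% power. One limit remains: T1 precedes the resident's own PEARL sessions but follows the facility's allocation, so T1 medication should also be tabulated by arm.

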We aim to recruit 308 participants from 22 RAC facilities. Additional facilities will be recruited if the target sample size is not reached working with 22 facilities. Estimations were based on expectations of *k* = 22 facilities, with an average of 14 participants each (*n* = 308), adjusted to allow for: (i) a within-cluster correlation, reflected in an intra-class correlation of .054, and (ii) attrition rate of 25% over 6 months, based on previous Australian longitudinal samples in RAC [17, 18]. The final sample of *n* = 231 participants at the primary endpoint (6 months post-baseline) will provide 80% power to detect a moderate effect in depressive symptoms (d = .48) [19], with 5% Type I error (two-sided). The moderately small effect size approximately corresponds to r-square of 0.05 (i.e., the intervention explains at least 5% of variance in depressive symptoms). The selected effect size was based on meta-analyses of psychological interventions for depression with older adults, which reported overall mean effect sizes of g = 0.64 [20] and g = 0.57 [7]. Figure 1 is a CONSORT flow diagram of participants in the trial.

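### The three-level model names no facility-by-time term, so the 5% error of the group-by-time test is not assured when facilities are randomised

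*Protocol article*

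**What the plan says.** The Statistical analysis section of the protocol article sets a separate three-level model for each outcome, "with repeated measurements as level 1, individuals as level 2, and RAC facilities as level 3". Group, time and group by time are the predictors. Medication use at each visit, organisational climate and facility size are covariates. On the random part it says only: "Individual and RAC facility variables will be modelled as random effects and the remaining variables will be modelled as fixed effects". Time falls among the remaining variables. No facility-by-time effect or facility slope is named.

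The only stated error rate is in the sample-size paragraph (Sample population and recruitment procedure): the design "will provide 80% power to detect a moderate effect in depressive symptoms (d = .48") "with 5% Type I error (two-sided"). It rests on 22 "facilities, with an average of 14 participants each", "a within-cluster correlation, reflected in an intra-class correlation of .054", and an "attrition rate of 25% over 6 months". No ICC or variance is given for change over time.

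**The concern.** Allocation is by facility, so any test of the intervention needs an error term that includes variation between facilities. A facility random intercept supplies this for the level of the outcome at a visit. It does not do so for change: an intercept that is equal at T1 and T3 subtracts out of T3 minus T1, and so does the individual intercept. Only the occasion-level residual is left to judge the group-by-time contrast. Organisational climate and facility size do not help, since they are listed as covariates and not as interactions with time.

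The article's own description makes facility-specific change plausible. Facility staff put the agreed strategies into practice (Intervention). They are informants for both the Cornell Scale and the SCID-5-CV (Outcomes). Usual care is whatever the facility offers. If residents in one facility tend to improve or worsen together, the standard error of the interaction is too small, its interval too narrow and its false-positive rate above nominal.

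**Working it through.** **The plan's own figure.** Analysed sample: 308 × 0.75 = 231, or 231/22 = 10.5 per facility. With 14 per facility, the design effect is 1 + 13 × 0.054 = 1.702 and the effective n is 231/1.702 = 135.7. The noncentrality is 0.48 × √(135.7/4) = 2.80, and normal-theory power is 79.8%. The stated 80% reproduces.

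**Error of the T1-to-T3 group-by-time contrast, random intercepts only.** Set total variance to 1.

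- From the article: facility variance 0.054; 22 facilities, taken as 11 per arm; 10.5 to 14 residents per facility.
- Assumed: individual-intercept variance 0.5, so residual variance is 1 − 0.054 − 0.5 = 0.446.
- Assumed: a share f of the 0.054 is specific to the visit, so facility-by-time variance is 0.054f.

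The ICC of change is ρ = 0.054f / (0.054f + 0.446). The intercept-only model treats changes as independent, so true variance / model variance = 1 + (m − 1)ρ. The actual two-sided error is 2[1 − Φ(1.96/√ratio)].

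For f = 0.25: ρ = 0.0135/0.4595 = 0.0294. With m = 10.5 the ratio is 1 + 9.5 × 0.0294 = 1.279 and the error is 8.3%. With m = 14 the ratio is 1.382 and the error 9.5%.

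The simulations used 10,000 balanced runs with 22 facilities and four visits.

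| f | ρ | Ratio, m = 10.5 / 14 | Closed form | Simulated T3 contrast, m = 10 / 14 | Simulated joint 3-df test, m = 10 / 14 |
|---|---|---|---|---|---|
| 0 | 0 | 1 / 1 | 5.0% / 5.0% | 5.2% / 5.2% | 5.6% / 5.2% |
| 0.10 | 0.0120 | 1.114 / 1.156 | 6.3% / 6.8% | 6.5% / 6.9% | 7.1% / 8.1% |
| 0.25 | 0.0294 | 1.279 / 1.382 | 8.3% / 9.5% | 8.4% / 9.6% | 10.6% / 13.2% |
| 0.50 | 0.0571 | 1.542 / 1.742 | 11.5% / 13.8% | 11.1% / 13.7% | 16.3% / 21.5% |

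**Sensitivity to the person-level share.** With 0.3 to 0.7 in place of 0.5, and m from 10.5 to 14, the closed form gives 5.9-8.3% at f = 0.10, 7.3-13.0% at f = 0.25 and 9.5-19.5% at f = 0.50.

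**With dropout.** In 350 full three-level maximum likelihood fits with 25% dropout by T4 (Monte Carlo standard error 1 to 2 points), the T3 contrast rejected 3.1% at f = 0 and 13.1% at f = 0.50. The joint test rejected 18.9% at f = 0.50.

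**After the change.** Comparing facility mean changes on t with 20 df gave 4.8-5.2% in all the balanced scenarios. In the fits with dropout, REML with a facility-by-time effect and t on 20 df gave 2.0% at f = 0 and 4.0% at f = 0.50.

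**Power on 20 df, single endpoint.** With 10.5 analysed per facility the design effect is 1 + 9.5 × 0.054 = 1.513. The noncentrality is 0.48 × √(231/1.513/4) = 2.97, and power is 80.5%. If the design effect for 14 is kept, power on 20 df is 75.8%; but 10.5 is the size that goes with 231 analysed.

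**The case against.** The best defence is that this is a condensed article. It never uses the word intercept, its sentence on random effects is ambiguous, and it does not say which coefficient or test statistic decides the trial. Covariance structure, degrees of freedom and the choice of REML are commonly left to the analysis plan. That stands as a caution. But the article does more than stay silent: it says what is random and assigns everything else, time included, to the fixed part.

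The amount of facility-by-time variance is also unknown. Time runs from each resident's own baseline, so with staggered admissions a calendar shift in a facility would be spread across visits and need not become a facility-by-visit effect. This too stands. Facility differences in how residents settle, or in how staff apply the strategies, would still produce one.

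The stated 5% belongs to a sample-size calculation for one endpoint. That is correct, but the article gives no other level for its tests.

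Three stronger readings are tempting and are not supported:

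- A reader might infer that the error does exceed 5%. With parallel facility trajectories it is about 5%.
- A reader might blame maximum likelihood with only 22 facilities. Under intercepts only, the standard error of this contrast comes from within-person residuals, and the simulated error at f = 0 is 5.2%. The number of facilities matters for this test once a facility-by-time term is present.
- A reader might take conditional maximum likelihood as an estimator that removes person or facility effects and so cannot yield the group effect. The article uses the phrase for incomplete data: "missing data will be assumed to be missing at random and will be handled with conditional maximum likelihood estimation". In a paragraph that specifies random effects, loose wording for likelihood-based estimation is the more natural meaning.

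**Conclusion.** The point holds in conditional form. As written, and read as random intercepts, the model gives the group-by-time contrast no variance term at the level of randomisation, so the 5% two-sided error is not assured. The error is about 5% with no visit-specific facility variance. It is about 6.5-7%, 8-10% and 11-14% when 10%, 25% and 50% of the facility variance is visit-specific, and higher for a joint test over all visits. These figures rest on the article's ICC of .054 and 22 facilities, an assumed person-level variance share of 0.5, and 10 to 14 residents per facility. The documents do not show where in this range the trial lies.

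**What to change.** State in the analysis plan that the model for each continuous outcome includes a facility-by-time random effect, fitted by REML with Kenward-Roger or Satterthwaite degrees of freedom. A comparison of facility-level mean changes is an acceptable alternative. For MDD, use a mixed logistic model with the matching random structure and a small-sample correction. Reword the missing-data sentence as likelihood-based estimation under missing at random.

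The cost is plan wording and standard software options, plus somewhat wider intervals. At f = 0.25 the honest standard error is √1.279 = 1.13 to √1.382 = 1.18 times the intercept-only one. If facility-by-time variance is in fact nil, the test may be a little conservative, as the 2.0% above suggests. Power for the single-endpoint comparison in the sample-size paragraph is still about 80% (80.5% on 20 df). That figure does not carry over to the change contrast, whose power depends on variances the article does not give.

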### Outcomes

Data will be collected from the intervention and control participants at baseline (within 4 weeks of admission to the RAC facility, T1), 8 weeks after baseline (T2), 16 weeks after baseline (T3), and 31 weeks after baseline (T4) (see Table 2 for participant timeline). The primary endpoint is T3, which is 2 months post-intervention. The T4 data collection point equates to a six-month post-intervention follow-up.

**Table 2 Tab2:** Participant timeline

TIMEPOINT	Enrolment	T1	Intervention period	T2	T3	T4
	1–4 weeks prior to baseline	Baseline	Week 1, 2, 3, 5, 7	Week 8	Weeks 16	Week 31
Enrolment:						
Eligibility screen	X					
Informed consent	X					
Interventions:						
PEARL – 3 sessions, 2 boosters			X			
Care as usual control			X			
Assessments:						
Mini-Mental Status Examination	X					X
Cornell Scale		X		X	X	X
SCID-5-CD – Major depressive disorder		X		X	X	X
Geriatric Anxiety Scale		X		X	X	X
Quality of Life in Alzheimer’s Disease		X		X	X	X
DASS-21 – Stress scale		X		X	X	X
Index of Relocation Adjustment Scale		X		X	X	X
Instrumental Activities of Daily Living Scale		X		X	X	X
Basic Needs Satisfaction in Life Scale		X		X	X	X
Importance of Basic Needs Scale		X		X	X	X
Meaningful Activity in Residential Care Scale		X		X	X	X
View of Relocation Scale		X				
Medical and psychiatric conditions and treatment		X		X	X	X

*SCID-5-CV* Structured Clinical Interview for DSM-5 Disorders – Clinician Version

*DASS-21* Depression, Anxiety and Stress Scale-21

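### As written, the resident-level model implies one correlation across unequally spaced visits; if correlation falls with lag, T4 change-from-baseline contrasts of continuous outcomes are anti-conservative and T2 ones conservative

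*Protocol article*

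**What the plan says.** The protocol article, under Statistical analysis, sets one three-level model per outcome, "with repeated measurements as level 1, individuals as level 2, and RAC facilities as level 3". On the fixed part it says: "The models will include group allocation, assessment time, and group by time interaction as predictors", with medication use, organisational climate and facility size as covariates. It then divides the terms: "Individual and RAC facility variables will be modelled as random effects and the remaining variables will be modelled as fixed effects". Assessment time is one of the remaining variables, so the rule as stated leaves no room for a resident-specific slope. The section does not name a level-1 residual covariance or say whether time is categorical.

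Under Outcomes, follow-up is set at "8 weeks after baseline (T2), 16 weeks after baseline (T3), and 31 weeks after baseline (T4"). The six pairs of visits are therefore 8, 8, 15, 16, 23 and 31 weeks apart. The same section says: "The primary endpoint is T3, which is 2 months post-intervention". The sample size paragraph, under Sample population and recruitment procedure, instead refers to "participants at the primary endpoint (6 months post-baseline").

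**The concern.** A resident intercept with independent residuals implies a constant variance and a single correlation for all six pairs of visits (compound symmetry). The Background section describes depression already present at entry and new cases arising through the transition. In such a period, scores 8 weeks apart would plausibly agree more closely than scores 31 weeks apart. The fitted common correlation is then an average: too low for T1-T2 and too high for T1-T4. The standard error of a change from baseline depends directly on that correlation, so it would be overstated at T2 and understated at T4.

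What is at stake is mainly the T4 change contrast, where an understated standard error inflates the false-positive rate. The plan also relies on likelihood estimation under missing at random with 25% attrition expected. That approach leans on the covariance being right, although any resulting bias in the estimates was not quantified here.

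**Working it through.** **The plan's own figure.** The only related figure is the power statement: n = 231 "will provide 80% power to detect a moderate effect in depressive symptoms (d = .48"), "with 5% Type I error (two-sided"). It reproduces. 308 × 0.75 = 231; design effect 1 + (14 - 1) × 0.054 = 1.702; effective N = 231/1.702 = 135.7; power = Φ(0.48 × √(135.7/4) - 1.96) = Φ(0.836) ≈ 79.8%. With 10.5 completers per facility the design effect is 1.513 and power is 84.3% (normal) or 80.5% (t, 20 df). This calculation uses no within-resident correlation, so it does not help to choose one.

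**Formula.** Take complete data, equal variances and categorical time. The compound-symmetry fit estimates the mean r̄ of the six pairwise correlations. A constant facility intercept cancels from a change contrast. For the group-by-time contrast at visit j against baseline:

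- SE ratio (model/true) = √[(1 - r̄)/(1 - r(T1,Tj))]
- False-positive rate = 2 × [1 - Φ(1.96 × ratio)]

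**One case in full.** Suppose correlation falls linearly from 0.70 at 8 weeks to 0.50 at 31 weeks. The correlations at lags 8, 8, 15, 16, 23 and 31 are 0.700, 0.700, 0.639, 0.630, 0.570 and 0.500, so r̄ = 3.739/6 = 0.623.

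- T2: √(0.377/0.300) = 1.121, rate 2.8%
- T3: √(0.377/0.370) = 1.010, rate 4.8%
- T4: √(0.377/0.500) = 0.868, rate 8.9%

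**Range.** All correlations are assumptions.

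| Assumed pattern | r with T1 at T2 / T3 / T4 | r̄ | SE ratio T2 / T3 / T4 | False positives T2 / T3 / T4 |
|---|---|---|---|---|
| Constant 0.70 | .700 / .700 / .700 | .700 | 1.000 / 1.000 / 1.000 | 5.0 / 5.0 / 5.0% |
| Linear 0.7 to 0.6 | .700 / .665 / .600 | .662 | 1.062 / 1.005 / .920 | 3.7 / 4.9 / 7.1% |
| Linear 0.7 to 0.5 | .700 / .630 / .500 | .623 | 1.121 / 1.010 / .868 | 2.8 / 4.8 / 8.9% |
| Linear 0.8 to 0.5 | .800 / .696 / .500 | .685 | 1.255 / 1.018 / .794 | 1.4 / 4.6 / 12.0% |
| Stable plus decaying part | .700 / .580 / .469 | .593 | 1.165 / .985 / .876 | 2.2 / 5.4 / 8.6% |
| Exponential, 8-week r 0.6 | .600 / .360 / .138 | .385 | 1.240 / .980 / .844 | 1.5 / 5.5 / 9.8% |
| Exponential, 8-week r 0.9 | .900 / .810 / .665 | .806 | 1.394 / 1.011 / .761 | 0.6 / 4.7 / 13.6% |
| Baseline 0.5 with all later visits, later visits 0.75 with each other | .500 / .500 / .500 | .625 | .866 / .866 / .866 | 9.0 / 9.0 / 9.0% |

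A true resident-specific slope, tried at two assumed sizes, gave a milder result in the same direction: 4.1-4.5%, 4.7-4.8% and 6.1-7.0%.

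**With attrition and clustering.** This check used 22 facilities of 14, ICC 0.054 and monotone loss of 10%, 17% and 25% by T2, T3 and T4 (the first two figures assumed). Exponential decay with 8-week r of 0.7 to 0.9 gave change-contrast coverage of 98.7-99.3% at T2, 94.5-95.0% at T3 and 88.8-85.9% at T4. Linear decay from 0.7 to 0.5 gave 97.0%, 95.1% and 91.0%. In the same four cases, coverage for the between-arm difference at a single visit was 95.1-95.2% at T2, 95.0% at T3 and 94.5-94.7% at T4.

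**The case against.** The strongest reply is that the quoted sentence only sorts terms into random and fixed. It says nothing about the residual covariance, and a resident effect with fixed time is compatible with autoregressive or heterogeneous residuals. A statistical analysis plan that is not shown could supply these. This stands in part: a reader might infer that the plan forces a common correlation, and the text does not go that far. But the sentence assigns every remaining term, time included, to the fixed part. The published rule therefore excludes a random slope and points to the simple model. It is a stated choice that can be improved and not merely a detail left for later.

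A reader might also infer that T2 intervals are certainly too wide and T4 intervals too narrow. The documents do not support that. It requires correlation that falls with lag, categorical time, independent residuals and a change-from-baseline contrast, and none of these is stated. With constant correlation there is no error. If baseline alone is less correlated with later visits, which is also plausible just after admission, T2 and T3 become anti-conservative too.

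It is also fair to say that the harm depends on the contrast reported. Differences between arms at one visit hardly move, and the section does not say which contrast will be reported. Nor do the hypotheses make a claim specific to T2 or T4.

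**Conclusion.** The point holds in conditional form. On the natural reading, the stated model imposes one within-resident correlation on visits 8 to 31 weeks apart. Under the lag-decay correlation patterns tried, the change-from-baseline contrasts for continuous outcomes were conservative at T2 (about 1-4% false positives), close to nominal at T3 (4.6-5.5% with complete data) and anti-conservative at T4 (about 7-14%; 6-7% under the random-slope variant). T4 stayed anti-conservative, at about 9%, when only baseline was less correlated, and in that case T2 and T3 were equally affected.

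A reader might conclude that the primary result is compromised. If T3 is primary, as Outcomes says, lag decay hardly touches it. The point would weigh more if the primary endpoint were the 6-month point in the sample size paragraph, which lies nearest to T4. Those two statements contradict each other and must be reconciled, but that is a separate matter. This is a worthwhile refinement, not a threat to the trial. The figures concern continuous scores such as the Cornell scale; nothing was computed for binary MDD.

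**What to change.** In the Statistical analysis section, for continuous outcomes, replace the single resident intercept by an unstructured covariance over the four visits within resident, and keep facility as the cluster level. Name the fallback in advance if the model does not converge: heterogeneous Toeplitz, or spatial power in weeks. Unstructured should come first because it covers both falling correlation and a baseline visit that behaves differently; the fallbacks cover mainly the former.

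The cost is one sentence and no new data. The structure has 4 variances and 6 covariances, so 10 parameters with 308 residents, and little is lost if the correlation proves constant. The small downside is possible non-convergence, which the fallback covers. Binary MDD needs its own specification, because a within-resident residual covariance does not carry over directly to a multilevel logistic model.
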